### Outcome measures

#### Primary outcome

Time to union will be assessed with repeated CT scans in 2 weeks intervals from 6 to 16 weeks postoperative. If union is not achieved within 16 weeks, a CT scan will be made 24 weeks postoperatively. If union is not achieved at that point, the patient will be presented for another treatment modality. Union will be proclaimed and recorded when > 50% bone bridging occurs on CT scan [26, 27]. The Minimal clinically important differences (MCID) have not been defined. We use an arbitrary value of 3 weeks difference.

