## Complications and secondary surgery

We will record all complications related to the operative treatment (tendon, ligament, nerve or arterial injury, infection, complex regional pain syndrome, haematoma or hardware failure). Reoperations, defined as revision surgery and secondary surgery due to no union will be noted.

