## Protocol violations and patient drop-out

The patients evaluated for inclusion will be reported in a consort diagram (Fig. 3). The statistical analysis will be conducted on an intention-to-treat basis. Outcome scores will be analysed according to the initial study group assignment regardless of possible cross-over. If crossover does occur, a secondary per-protocol analysis will be conducted.

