**Fig. 3 Fig3:**
[figure not shown]
Consort flow diagram. Flow of patient through the study

Patients drop-out/loss to follow-up will be recorded and the reason will be noted. The patient is included in the analysis with their latest follow-up if at least a 6-week evaluation is available. Patients who undergo revision/secondary surgery will remain in the study and will be followed according to the index procedure. Their results before and after the revision procedure are included in the analysis. If challenges in the trial conduct occur, they will be presented by the primary investigator every second week to the research group. Any protocol modifications will be communicated to all investigators, observers and trial registries immediately. No regular audit is planned, apart from possible independent inspection visits by the Data Protection Agency and the National Committee on Health Research Ethics.

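### Results after revision surgery stay under the index procedure for every outcome, so a union reached after a second operation can be recorded for the randomised technique

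*Protocol article*

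**What the plan says.** The rule is in the protocol article under Protocol violations and patient drop-out, in the text after Fig. 3: "Patients who undergo revision/secondary surgery will remain in the study and will be followed according to the index procedure". The next sentence reads: "Their results before and after the revision procedure are included in the analysis". The same section sets the intention-to-treat principle: "Outcome scores will be analysed according to the initial study group assignment regardless of possible cross-over".

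The union outcomes are defined elsewhere:

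- **Primary outcome, schedule:** "Time to union will be assessed with repeated CT scans in 2 weeks intervals from 6 to 16 weeks postoperative", and then "If union is not achieved within 16 weeks, a CT scan will be made 24 weeks postoperatively".
- **Primary outcome, event:** "Union will be proclaimed and recorded when > 50% bone bridging occurs on CT scan". The definition does not mention which operation produced the bridging.
- **Primary outcome, after a failed week-24 scan:** "If union is not achieved at that point, the patient will be presented for another treatment modality".
- **Secondary outcomes:** union rate is read from the two-weekly CTs with no closing time point. DCA and HLR are read on CT before surgery and at an undated follow-up.
- **Complications and secondary surgery:** "Reoperations, defined as revision surgery and secondary surgery due to no union will be noted".

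**The concern.** The hypothesis is that one reconstruction technique heals the scaphoid faster than the other. If the scaphoid unites only after another operation, the first reconstruction did not achieve union. The rule on revised patients nevertheless admits post-revision results for all outcomes, and neither the union definition nor the union-rate description limits it. Followed as written, it can turn a failure of the index procedure into a union with a date, on a clock that started at the first operation.

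The arm with more failures gains most from this. The error therefore runs towards no difference, and it is largest when the techniques really do differ in failures. The per-protocol analysis does not correct it, because it removes patients who do not comply with the protocol, and needing a revision is not non-compliance.

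**Working it through.** The protocol states no figure for this point, so none can be reproduced. The check compares the rule with the CT schedule and then sizes the effect.

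**1. When the scheduled scans end.** Weeks 6, 8, 10, 12, 14 and 16 give six CTs, and week 24 gives a seventh. The Discussion agrees: up to 7 scans at 0.03 mSv, and 7 × 0.03 = 0.21 mSv, its stated maximum. The last scheduled union CT is therefore at week 24 (day 168).

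**2. Revision before week 24.** The complications section anticipates hardware failure and infection, either of which could lead to early revision. Take, as an illustration, a revision at week 10. The remaining scheduled CTs are at weeks 12, 14, 16 and, if still not united, 24. Bridging at week 16 would be recorded as union at 16 × 7 = 112 days, of which 70 precede the second operation and 42 follow it.

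- *Union rate:* one such patient adds 1/44 = 2.3 points to the arm.
- *Time to union:* if the patient were instead given the week-24 value, the difference is 168 − 112 = 56 days, or 56/44 = 1.3 days on the arm mean. If union is read at week 12 (84 days), it is 84/44 = 1.9 days. If it is read at week 24, the difference is 0 days and only the event status changes. The planned difference is 77 − 56 = 21 days.

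These figures assume all 44 patients per arm are analysed.

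**3. Revision after week 24.** A patient treated again because the week-24 CT showed no union has already been recorded as not united at every scheduled scan. Time to union is then no longer exposed. The union rate is, because it has no cut-off, but only if an unscheduled CT is taken. The Discussion says that departmental follow-up normally runs until union, so such scans are possible, but the protocol does not plan them.

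**4. Upper bound for the union rate.** Assume that every non-union is revised and every later union is counted. With index union rate p and revision success s, the reported rate is p + (1 − p)s, and a gap between arms shrinks by the factor (1 − s). The documents give no revision success rate. I take s = 77% to 94%, borrowing the Background's K-wire and screw union rates as a range.

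| Index rates | Index gap | Reported, s = 77% | Reported, s = 94% |
|---|---|---|---|
| 86% v 97% | 11 points | 96.8% v 99.3%, gap 2.5 | 99.2% v 99.8%, gap 0.7 |
| 96% v 97% | 1 point | 99.1% v 99.3%, gap 0.2 | 99.8% v 99.8%, gap 0.1 |

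The 86% is the low end of the arthroscopic series cited in the Background. The 96% v 97% comes from the one arthroscopic-versus-open comparison for which the Background reports union rates. In patients per 44, 86% means about 6.2 non-unions, 96% about 1.8 and 97% about 1.3.

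**The case against.** The strongest reply is that the protocol nowhere says a post-revision union counts as a union of the randomised technique. Results before and after a revision most naturally describes repeated measures such as Q-DASH or grip strength, since a patient has only one time to union. Reoperation for lack of union is also recorded separately. Analysing by assignment whatever happens later is a recognised treatment-policy choice, and detailed event rules often sit in a statistical analysis plan, which is not shown here.

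Part of this stands. The crediting of later unions follows from unqualified wording and is not an explicit statement. The rule is appropriate for the functional outcomes. For time to union, a revised patient still carries the delay since the index operation, so the failing arm is penalised to some extent.

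It does not remove the point. The rule is stated and exempts nothing, so an analysis plan that treated revision as failure of union would contradict it. Noting a reoperation does not stop a later CT from registering union. Counting the patient as not united with the index procedure is still analysis by assignment, because nobody is excluded or moved.

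A reader might also infer that non-unions at week 24 flow routinely into the primary outcome, or that a gap such as 86% v 98% could vanish into 100% v 100%. The documents support neither. Re-treatment for non-union comes after the last scheduled scan. The second result would need every failure to be revised, to unite and to be scanned, with 100% revision success.

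**Conclusion.** The point holds in a limited form. As written, post-revision CT findings enter time to union, union rate and DCA/HLR under the index procedure. The primary outcome is exposed mainly through revisions before week 24. After that only the union rate is exposed, through unscheduled scans.

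The number of patients is probably small, but this is a judgement, since the documents give no frequency of early revision. Each such patient is worth 2.3 points of union rate and, in the week-10 illustration, 0 to 1.9 days on an arm's mean. If the arms resemble the 96% v 97% comparison, hardly anything changes. If they differ as much as 86% v 97%, the upper bound is a gap cut from 11 points to between 2.5 and 0.7. That bound rests on the assumed 77–94% revision success and on every failure being revised and scanned. Because the rule affects how the primary event is defined, it should be settled before outcome data are examined, but it does not threaten the trial as a whole.

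**What to change.** Reconcile the rule on revised patients with the Primary outcome and Secondary outcomes sections:

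- **Patient-reported, pain, strength and motion outcomes:** keep the rule as it is.
- **Union rate and DCA/HLR:** fix the union-rate cut-off at the week-24 CT. State that revision or secondary surgery before union counts as not united with the index procedure, and that later CT findings are reported only as supplementary.
- **Time to union:** keep the patient in the assigned arm as not united through week 24, and take no union date from the revision. Handle this with a time-to-event analysis, or with a censored or worst-rank value at week 24.

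The first two changes cost a few sentences and no new data, because reoperations are already recorded. Reported union rates may be slightly lower. The third costs more. The sample size is built on a difference in means and the primary analysis is a mixed effect model, which gives a patient without a union time no value. The primary analysis must therefore be specified so that it can accommodate such patients.

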## Adverse events

The operative techniques are used routinely in our department and are considered safe, therefore interim analysis will not be conducted. At follow-up, patients will be asked about complications, and journal notes about hospital contacts related to the surgical procedure are recorded.

### Statistics

#### Sample size calculation

The sample size calculation was performed with an expected mean time to union of 56 days and a SD of 30 days in Group A and 77 days and SD on 40 days in group B. The sample size required in each group to provide 80% power to detect a mean 3 weeks difference [13], with two-sided alpha on 0.05, was 36 patients in each group. Considering dropouts and loss to follow-up with a rate of 20% the final number of patients needed in total for this study is 88 patients.

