### Hypothesis

Arthroscopic assisted C chips graft reconstruction of scaphoid delayed/non-union is superior to open C graft reconstruction regarding faster time to union, by at least a mean 3 weeks difference.

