We aim to decrease observer and selection bias through blinding and randomization, stratified for tobacco-smoking habits, fracture displacement (> / < 2 mm) and proximal pole fractures. By adding 20% to the sample size, we compensate for dropouts and attempt to avoid Type-II errors. Potential dropouts will be minimized with permission to contact patients by mail or phone if they do not show up for follow up-visit or if data is missing.

The patients will not be blinded to their treatment allocation. Sham surgery can be used to blind patients regarding skin incisions and subsequently the surgical technique. However, all patients treated with open bone grafting using a cancellous graft taken from the iliac crest will be operated on in general anaesthesia, while arthroscopically treated patients undergoing the treatment in regional block anaesthesia. Furthermore, the use of graft from the iliac crest in one group and not the other makes it difficult to blind patients as donor-side pain is expected. Finally, we do not expect patients to have an expectation of open- or arthroscopic-assisted graft reconstruction to be superior to the other.

Observer bias is minimized with a blinded musculoskeletal radiologist for the primary outcome, to prevent observer bias from favouring one of the interventions.

The secondary outcome (Q-DASH) is reported by the patient independently, thus with no implication to the assessor. Other secondary outcomes are evaluated by an independent, non-blinded observer.

The current standard treatment at our department includes follow-up until the union is established. In this study, we will have additional follow-up examinations at 6 months and at 1 and 2 years. It has the risk of keeping the patients in the role of being ill. However, the patients can have a feeling of extra good care with the possibility to address uncertainty or problems more easily.

Patients are at risk of being treated inferior with an intervention which is deemed inferior with the study analysis, but nothing a priori suggests which intervention is the better one.

The trial will provide high-quality evidence regarding time to union and short- and long-term functional outcomes of open and arthroscopic assisted graft reconstruction for scaphoid delayed/non-union.

The results from the study can contribute to establish a treatment algorithm for scaphoid delayed/non-union together with results from other studies.

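### The stated inputs need 45 to 46 evaluable patients per group, not 36; at 36 the two-sided power is about 70%, not 80%

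*Protocol article*

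**What the plan says.** The Sample size calculation section gives every input: "expected mean time to union of 56 days and a SD of 30 days in Group A" and, for the control arm (labelled B there and O elsewhere), "77 days and SD on 40 days in group B". The target is "80% power to detect a mean 3 weeks difference", and the result, "with two-sided alpha on 0.05, was 36 patients in each group". After a 20% allowance for dropout, "the final number of patients needed in total for this study is 88 patients". The Randomization section fixes 1:1 allocation.

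The Discussion describes the allowance: "By adding 20% to the sample size, we compensate for dropouts and attempt to avoid Type-II errors". The Hypothesis section states superiority "by at least a mean 3 weeks difference", and the Abstract words it the same way. The Data analysis section applies a 5% significance level throughout and mentions no one-sided test.

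**The concern.** All the inputs are printed, so the result can be checked without assumptions, and 36 does not follow from them. The gap is 9 to 10 patients per group, too large for rounding or a difference between software packages.

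At stake is how a non-significant primary result is read. A reader who trusts 80% power takes the chance of missing a true 3-week difference as one in five; on the stated inputs it is closer to three in ten. The dropout allowance is built on the same 36, so it does not protect 80% power either.

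**Working it through.** **Inputs** (Sample size calculation section): difference 77 − 56 = 21 days; variances 30² + 40² = 2500; power 80%; two-sided alpha 0.05; equal groups.

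**Trying to reproduce 36.** Formula: n per group = (z for alpha + z for power)² × (SD₁² + SD₂²) / difference².

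- Two-sided 0.05, 80% power: (1.960 + 0.842)² × 2500 / 441 = 44.5, so 45. With the noncentral t, pooled or Welch: 46.
- One-sided 0.05, 80% power: (1.645 + 0.842)² × 2500 / 441 = 35.05, so 36. The t-test also gives 36. Two-sided alpha 0.10 uses the same critical value and gives 36.
- Two-sided 0.05, 70% power: the pooled t-test gives 68.8% at 35 per group and 70.03% at 36, so 36 is the smallest number that reaches 70%.
- Other two-sided variants at 80% power: average SD of 35, 44 to 45; SD 30 in both arms, 33; SD 40 in both arms, 57; Wilcoxon efficiency 0.955, about 48. None gives 36.

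**Power at the numbers in play.** SE = √(2500/n); normal-approximation power = Φ(21/SE − 1.960). At n = 36, SE = 8.33 and 21/8.33 − 1.960 = 0.56.

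| Analysed per group | Situation | Normal | Welch t |
|---|---|---|---|
| 35 | 88 × 0.8 / 2 = 35.2 | 70.0% | 68.7% |
| 36 | as stated | 71.2% | 69.9% |
| 44 | no losses | 79.6% | 78.6% |

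**Difference detectable with 80% power** (2.802 × SE by the normal formula): at 36 per group, 23.3 days (23.7 by Welch t); at 35 per group, 23.7 days (24.0 by Welch t).

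**Dropout step.** 36 × 1.2 = 43.2, so 44 per group and 88 in total, which matches the document. Dividing by the retained fraction gives 36 / 0.8 = 45 per group and 90 in total. The difference is one patient per group.

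**Smallest significant difference at 36 per group.** 1.96 × 8.33 = 16.3 days, or 16.6 days with the t critical value.

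**The case against.** Four arguments can be made for the plan.

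1. *The analysis is not an unadjusted t-test.* The Data analysis section adjusts for the three stratification factors, partly to gain power. That is a real benefit, but the sample size section claims none of it. To reach 80% at 36 per group, the covariates would have to explain 1 − (21/2.802)² × 36/2500 ≈ 19% of the variance (about 21% by t). With all 44 analysed, 1% to 3% would do. The article gives no such figure. The argument therefore stands as a limit on the claim: the calculation as written lacks 80% power, while the power of the adjusted analysis is unknown.

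2. *The 20% loss may not fall on the primary endpoint.* The CT series ends at 16 weeks (24 if not united), whereas follow-up runs for years. Patients with at least a 6-week evaluation stay in the analysis, and multiple imputation is planned. This is fair: 35 per group is what the protocol's own allowance implies, not a forecast. But even 44 per group gives only about 79% to 80%.

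3. *The dropout method is disclosed and its effect is small.* Agreed. It is one patient per group and about one point of power, and would not merit a finding alone.

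4. *The 3 weeks can be read as the difference to detect.* The Primary outcome section calls it an arbitrary value in the absence of a defined MCID. Any conventional superiority test can reach significance below its planning difference, so this is a wording issue and not an arithmetic error.

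A reader might also infer that 36 is a one-sided calculation mislabelled as two-sided. The number fits, but it fits 70% power at two-sided 0.05 as well, and the document does not settle which.

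**Conclusion.** The point holds. On the protocol's own inputs, 80% power at two-sided 0.05 needs 45 (normal) or 46 (t-test) evaluable patients per group. The stated 36 gives about 70% to 71%, the protocol's assumed loss from 88 gives 69% to 70%, and full retention gives about 79% to 80%. These figures rest on the printed means and SDs, equal groups and an unadjusted comparison of means.

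It would go too far to say that the trial cannot have 80% power. With little loss and a modest adjustment gain it could come close to 80% or pass it, but the article neither makes nor supports that case. The cause of the slip is unknown, and the dropout step is minor.

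The hypothesis wording is secondary. The calculation is against zero, and an observed difference of about 16 to 17 days would already be significant at 36 per group. Significance alone therefore would not show a benefit of 3 weeks or more.

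**What to change.** Keep 88 patients and two-sided alpha 0.05, and correct the text.

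- **Sample size calculation.** Suggested wording: *For a 21-day difference (SD 30 and 40 days, two-sided alpha 0.05), 80% power requires 45 to 46 evaluable patients per group. With 88 randomised and 20% lost (about 35 per group), the unadjusted comparison has about 69–70% power, and about 79% with no losses. The difference detectable with 80% power is about 23.5 days at 36 per group and about 24 days at 35.*
- **Covariate adjustment.** If a power gain is to be claimed, state the assumed proportion of variance explained and its basis.
- **Discussion.** Amend the sentence on adding 20% so that it no longer implies that the allowance secures the intended type II error. Do not describe 88 as 36 divided by 0.8, which is 45 per group and 90 in total.
- **Hypothesis and Abstract.** State the hypothesis as faster time to union, with 3 weeks as the planning difference, and judge clinical relevance by where the confidence interval lies relative to 21 days.

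The cost is wording and a less favourable power figure, with no extra patients. If the sponsor wants 80% power after 20% loss without relying on adjustment, the number is 45/0.8 to 46/0.8, rounded up to 57 to 58 per group, or 114 to 116 randomised. That is 26 to 28 more than planned.

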## Randomization

Based on the sample size calculation, a total number of 88 patients will be allocated into two groups of equal size.Group A – Arthroscopic assisted C chips graft reconstruction (intervention group), *N* = 44.Group O – Open C graft reconstruction (control group), *N* = 44.

The randomization is done in the outpatient clinic and the patients will be informed about the operative treatment. The randomization is done using an irreversible application in Research Electronic Data Capture (REDCap). Patients will be allocated in a 1:1 ratio by block randomization, stratified for proximal pole fracture (yes /no), dislocation (> / < 2 mm) and smoking (yes/ no). An independent statistician generated the randomization sequence for REDCap, and thus the allocation is concealed to the research staff and physicians.

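### The 20% drop-out allowance is added (36 × 1.2) rather than divided out (36 / 0.80), so 88 patients cover about 18% loss, not 20%; a minor error, to be corrected together with the base number

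*Protocol article*

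**What the plan says.** In the protocol article, Statistics – Sample size calculation, the assumption for the arthroscopic arm is "expected mean time to union of 56 days and a SD of 30 days in Group A". For the comparator, called Group O elsewhere, it is 77 days with an SD of 40. The target is "80% power to detect a mean 3 weeks difference", and the significance level is 0.05, two-sided. The section reports 36 patients per group, then makes an allowance for patients who are lost: "with a rate of 20% the final number of patients needed in total for this study is 88 patients".

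The Discussion says how the allowance was made: "By adding 20% to the sample size, we compensate for dropouts and attempt to avoid Type-II errors". The Randomization section carries the total forward: "Based on the sample size calculation, a total number of 88 patients will be allocated into two groups of equal size". Both that section and Subjects give 44 per group.

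Two other sections bear on what a lost patient means for the analysis. Protocol violations and patient drop-out keeps a patient in the analysis at the latest follow-up, provided a 6-week evaluation exists. Data analysis specifies intention-to-treat for the primary outcome and multiple imputation for missing outcome data.

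**The concern.** The plan states three figures: 36 needed per group, a loss rate of 20%, and 88 in total. They do not fit together. A loss rate applies to the patients who enter the trial, so protecting a required number against it means dividing by the proportion retained. Adding the same percentage to the required number always falls short, because 1.2 × 0.8 = 0.96.

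At stake is a published statement that the total compensates for 20% loss when it compensates for slightly less. The direct effect is small. The method matters more if the base number is revised, because the same multiplication would then leave a larger shortfall.

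**Working it through.** **Inputs** (all from Sample size calculation, except the method of allowance, which is from the Discussion): means 56 and 77 days, so a difference of 21 days; SDs 30 and 40 days; power 80%; two-sided alpha 0.05; 36 per group; loss 20%; total 88; 20% added to the sample size.

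**Step 1: reproduce the plan's total.** 36 × 1.2 = 43.2, rounded up to 44 per group; 2 × 44 = 88. This matches the stated total and the group sizes.

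**Step 2: apply 20% loss to 88.** 88 × 0.80 = 70.4 in total, or 44 × 0.80 = 35.2 per group. The stated requirement is 2 × 36 = 72. The shortfall is 0.8 patient per group.

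**Step 3: the division.** 36 / 0.80 = 45 per group, 90 in total. Check: 90 × 0.80 = 72.

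**Step 4: the loss that 88 does cover.** 1 − 72/88 = 18.2%. Per group, 44 − 36 = 8 patients can be lost, and 8/44 = 18.2%.

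**Step 5: effect on power.** With n per group, SE = √((30² + 40²)/n) = √(2500/n), and two-sided power is approximately Φ(21/SE − 1.96).
- n = 36: SE = 8.33; 21/8.33 = 2.52; power = Φ(0.56) = 71.2%.
- n = 35: SE = 8.45; 21/8.45 = 2.48; power = Φ(0.52) = 70.0%.

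The unequal-variance t-test (non-central t) gives 69.9% and 68.7%. Either way the step from 36 to 35 costs about 1.2 points.

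**Step 6: the base number.** The stated inputs give n = (1.96 + 0.842)² × 2500 / 21² = 44.5, so 45 per group, or 46 with the t-test. They do not give 36. A one-sided alpha of 0.05 gives (1.645 + 0.842)² × 2500 / 441 = 35.1, so 36, but the plan states a two-sided alpha.

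| Patients per group with data | Two-sided power, normal approximation | Two-sided power, unequal-variance t |
|---|---|---|
| 35 (88 randomised, 20% loss, rounded down) | 70.0% | 68.7% |
| 36 (90 randomised, 20% loss) | 71.2% | 69.9% |
| 44 (88 randomised, no loss) | 79.6% | 78.6% |
| 45 | 80.4% | 79.5% |
| 46 | 81.3% | 80.4% |

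**Step 7: why the method still matters after the base is corrected.**
- From 45: × 1.2 gives 54 per group (108 in total); / 0.80 gives 56.25, so 57 (114).
- From 46: × 1.2 gives 55.2, so 56 (112); / 0.80 gives 57.5, so 58 (116).

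Keeping the multiplication would leave a corrected trial 4 to 6 patients short.

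**The case against.** The strongest objection is that the gap has no practical weight. It is 88 against 90, two patients. The unrounded deficit is 0.8 patient per group, and 20% is itself a round planning guess. No decision about the trial turns on 18% versus 20%. This stands, and it is why the point is minor.

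A second objection concerns what happens to lost patients. A reader might infer that 88 randomised patients leave only 35 per group to analyse. The documents do not support that. A patient lost after week 6 stays in the analysis, missing outcomes are imputed, and the primary analysis is adjusted for the stratification factors partly to gain power, a gain that the stated calculation shows no sign of counting. The 35.2 is therefore a count of patients with complete follow-up, not of patients analysed. The softening is only partial. Week 6 is the first CT of a series that runs to week 16, so a patient lost then without union has no observed time to union, and imputation from the listed baseline covariates recovers little of that information. Patients found ineligible at surgery, after allocation, are also to be excluded, and the calculation names no separate allowance for them.

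A third objection is that 36 is the wrong yardstick. This stands too. With the stated inputs 36 gives about 70% power, so falling below 36 means moving from about 70% to about 69%. A reader might infer that raising the total to 90 would secure the stated 80%. It would not: 90 with 20% loss returns 36 per group and about 70%.

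**Conclusion.** The allowance is wrong as written, and the error is minor. The stated requirement, loss rate and total cannot all hold: 88 keeps 36 per group with complete follow-up up to 18.2% loss, and at 20% it leaves 35.2. The cost is about one point of power, partly offset by the rules that retain or impute incomplete patients.

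This rests on the plan's SDs of 30 and 40 days, a difference of 21 days, equal loss in both groups, and the 20% being a share of those randomised, which is the natural meaning of a loss rate.

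It does not show that the drop-out step by itself leaves the trial materially underpowered. The larger gap in the same paragraph is the base number: 36 does not follow from the stated two-sided inputs, which require 45 to 46 per group before loss. Neither 88 nor 90 with 20% loss delivers the stated 80%.

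**What to change.** In Sample size calculation, keep 88 and state that it covers up to about 18% loss relative to the stated 36 per group. In the Discussion, replace the description of adding 20% with division of the required number by one minus the expected loss.

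Make this edit together with the correction of the base number, and restate the power. If 88 is kept, the text should say that 36 per group gives about 70% power at two-sided alpha 0.05 under the stated SDs and difference; it should not present 36 as sufficient for 80%. If the base number is revised instead, apply the division to the new figure: 45 or 46 per group with 20% loss gives 114 or 116 in total, and the 18% and 90 figures then no longer apply.

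The drop-out edit alone costs two sentences and no patients, and the tolerated loss reads slightly less favourably. Restating the power also needs no patients. Only keeping both 80% power and 20% loss would add any: 26 to 28 more than 88.
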